**Table 1: Schedule of Assessments**

| Monitoring during SCN stay                                              | Corrected gestational age (weeks) |    |                                 |         |
|-------------------------------------------------------------------------|-----------------------------------|----|---------------------------------|---------|
|                                                                         | 33                                | 34 | 35                              | 36+     |
| Breastfeed (usual condition for each baby)                              | ✓                                 |    | ✓                               | Invited |
| Breastfeed: full breast                                                 |                                   | ✓  |                                 |         |
| Breastfeed: empty breast                                                |                                   | ✓  |                                 |         |
| Breastfeed: nipple shield                                               |                                   |    |                                 |         |
| Breastfeed: no nipple shield                                            |                                   |    | Invited if shield normally used |         |
| Bottlefeed: allocated conventional / Calmita teat                       | ✓                                 | ✓  | ✓                               | Invited |
| Maternal 24hr milk production study                                     | ✓                                 | ✓  | ✓                               |         |
| Pre and post weighs with every breastfeed                               | Throughout SCN stay               |    |                                 |         |
| Oral feeds with allocated teat where mother not available to breastfeed | Throughout SCN stay               |    |                                 |         |
| Monitoring post discharge                                               | Corrected postnatal age (weeks)   |    |                                 |         |
|                                                                         | term                              | 2  | 6                               | 12      |
| Breastfeed (usual condition for each baby)                              | ✓                                 |    |                                 |         |
| Follow up phone call                                                    |                                   | ✓  | ✓                               | ✓       |

[figure not shown]

**Figure 1. Study Design**

## Source and Selection of Participants

Participants will be recruited from the Special Care Nurseries at KEMH. We will recruit 60 mothers and their healthy preterm infants born between 28-33 weeks gestation with a home address within a 35km radius of the hospital.

*Inclusion criteria* will include medically stable infants, and mothers with an intention to breastfeed and total daily breastmilk expression volume of at least 300 mL/24hr.

*Exclusion criteria* will include mothers with a history of breast surgery, infants receiving CPAP or mechanical ventilation at 34 weeks CGA, acute illness and/or infection and congenital disease or malformation.

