#### Trial Plan:

A randomised controlled trial of 60 preterm infants will be carried out. When an infant is ready for a suck feed but mother is unable to be present, bottle feeds will be given using a conventional teat (control group) or Calmita teat (intervention group). Weekly breastfeeds and bottle-feeds will be monitored for SSB coordination, heart rate, oxygen saturation and milk intake. Infants will have a single breastfeed monitored at 33 weeks CGA, and up to 2 breastfeeds monitored over 2 consecutive days at 34 weeks CGA (breastfeeds from 'full' and 'empty' breasts) and at 35 weeks CGA (with and without a nipple shield). The intervention group will be given the Calma teat (term version of Calmita) at discharge from the study hospital.

Breastfeeding outcomes will be tracked by follow up phone calls up to 3 months post term.

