### Trial Design

#### Trial endpoints

The primary endpoint for this trial is total breastfeed volume (mL) transferred at a breastfeed, measured at 33, 34, 35 weeks and term CGA

Secondary endpoints to be measured during monitored feeds are  
efficiency (mL/min)

- total suck duration

- total suck bursts
- mean, peak and baseline intraoral vacuum (mmHg)
- oxygen saturation range
- heart rate range
- incidence of bradycardia
- incidence of oxygen desaturation

The following feeding endpoints will also be determined

- timing of achievement of full oral feeds
- timing of achievement of full breastfeeding
- breastfeeding duration (monitored up to 3 months post-term)

1. A randomized controlled clinical trial will be undertaken with random allocation in blocks of size 4 to either a control group or an intervention group. Study design is depicted in Figure 1.
2. A pilot study of up to 5 infants will be completed prior to commencement of the trial to test and refine the set-up and duration of monitoring sessions.
3. Study participant data and milk samples will be re-identifiable, with an identification code assigned to each infant. A master sheet that matches infant identity to identification codes will be stored in a password-protected electronic file on a lap top computer. All paper copies of case report forms will be stored in a locked filing cabinet at The University of Western Australia.
4. The effect of a vacuum-controlled bottle-feeding teat (Calmita and Calma teats, Medela AG) on breastfeeding outcomes will be evaluated in this clinical trial. A shut-off valve is incorporated into the Calmita teat so milk flows only when the infant creates a vacuum. Venting prevents collapse of the teat. There are two versions of Calmita with different threshold levels for the vacuum-controlled valve of  $-10 \pm 5$  mmHg (starter teat) and  $-30 \pm 15$  mmHg (advanced teat). We have previously investigated a prototype of this product but wish to carry out more extensive studies on the final product.

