## Treatment of Participants

1. When the mother is not available to breastfeed, control group infants will use a conventional teat for suck feeds whereas the interventional group infants will use the Calmita teat. The starter teat will be offered initially and when the infant takes full feeds from the starter teat for 48-72 hours they will then use the advanced teat.
2. Monitoring of a weekly breastfeeds and bottle feeds with the allocated teat will be performed at 33, 34 and 35 weeks CGA and involves the following
  - Weigh infant pre and post breastfeeding
  - Intraoral ultrasound
  - Continuous Intraoral vacuum measurements
  - Respiratory Inductive plethysmography
  - Continuous pulse oximetry for oxygen saturation (SaO2) and heart rate
  - (optional) Maternal pre/post breastfeed milk samples <1.0mL
  - Maternal rating of Preterm Infant Breastfeeding Behavior Scale[5] (PIBBS, Appendix A)

SSB coordination is evaluated using data from intraoral vacuum, respiration and swallowing (Respiratory Inductive Plethysmography) heart rate and oxygen saturation obtained throughout the entire breastfeed[6].

3. Test weights of the infant pre and post feed, for all feeds, will be made to determine milk intake and allow calculation of top up feeds. For monitored feeds, pre and post feed milk samples (<1.0mL) will be collected and fat content measured to provide a further estimate of breast fullness.
4. At each monitored breastfeed the Preterm Infant Breastfeeding Behavior Scale[5] (PIBBS, Appendix A) will be completed by the mother.
5. In the study setting it is assumed that most stable preterm infants are offered (at least daily) breastfeeding experiences from 32 weeks CGA. A weekly breastfeed will be monitored from 33 weeks CGA. At 34 weeks CGA each infant will have up to 2 breastfeeds and one bottle-feed monitored in random order on 2-3 consecutive days with a full or empty breast. A full breast is one that has not been expressed for 3 hours prior to feeding and an empty breast one that has been expressed within an hour of the feed. At 35 weeks CGA those using a nipple shield will have the option of also having a monitored breastfeed without a nipple shield.
6. At 35 weeks or at discharge/transfer each infant will have 1 breastfeed monitored with or without a nipple shield depending on whether the infant is typically feeding with a shield, and one bottle-feed will be monitored. Infants

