### Statistical analysis, data management, and record keeping

The primary outcome measure for this study is the total volume transferred during a breastfeed. Meier reported average transfer volumes of  $18.4\text{mL} \pm 13.2$  and  $3.9\text{mL} \pm 7.0$  with and without nipple shield, respectively [11]. Samples sizes required to detect a clinically relevant effect of 5mL difference between feeds with full and empty breasts were calculated separately for these two conditions. The more conservative calculation is that the study would need 24 infants in each treatment group to have 80% power (Type I error rate  $\alpha=0.05$ ) of detecting a difference this large. Allowing for a possible dropout rate of 20%, as was observed in a similar study, 30 infants per group will need to be recruited at 33 weeks CGA. The sample size was calculated as if the data will be analysed using an independent samples *t*-test. Actual analyses will be more powerful, and thus will have power to detect smaller differences.

Using this sample size, an independent samples *t* test would have the power to detect differences in secondary outcomes equivalent to  $0.83 * \text{SD}$ . This is equivalent to differences of approximately 3.9 min total sucking duration, and 12 suck bursts per feed. As with the primary outcome, use of covariate data, repeated measurements and more powerful analytic techniques increase the likelihood of detecting smaller differences than those determined here.

Data will be analysed on an intention to treat basis using R 2.15 or later versions (The R Core Team)[12] with nlme,[13] lattice,[14] and multcomp[15] packages for linear mixed models, graphical exploration and general linear hypothesis tests, respectively. To monitor both safety and efficacy, interim analysis will be performed when complete data is available for 15 infants in each group, with p values set to  $p=0.029$  for both interim and final analyses as per Pocock (p372, [16]).

For the monitored breastfeeds, differences in milk transfer volume as well as measured sucking, physiological, and feeding variables, linear mixed effects modelling will be used, with grouping for the random effects at the participant level. Use of nipple shield (yes/no), breast fullness (full/empty) and relevant demographic variables will be considered as predictive factors.

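### The CPAP/ventilation exclusion is dated 34 weeks, after allocation appears to have taken place, and the fixed blocks of 4 have no described concealment

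*Combined protocol and SAP*

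**What the plan says.** **Timing of eligibility and allocation.** Source and Selection of Participants lists as an exclusion "infants receiving CPAP or mechanical ventilation at 34 weeks CGA". The statistical analysis section says that "30 infants per group will need to be recruited at 33 weeks CGA". Treatment of Participants, item 2, states: "Monitoring of a weekly breastfeeds and bottle feeds with the allocated teat will be performed at 33, 34 and 35 weeks CGA". Table 1 agrees: its row "Bottlefeed: allocated conventional / Calmita teat" is ticked at 33, 34 and 35 weeks. Under Trial endpoints, the primary endpoint is "measured at 33, 34, 35 weeks and term CGA".

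**Analysis population.** The statistical analysis section states: "Data will be analysed on an intention to treat basis". It does not say how an allocated infant who meets the 34-week exclusion is handled.

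**Allocation method.** Trial Design, item 1, specifies "random allocation in blocks of size 4 to either a control group or an intervention group". The Trial Plan gives the size: "A randomised controlled trial of 60 preterm infants will be carried out". Recruitment is at one hospital. The readable text describes no varied block size, no custody of the sequence and no concealment.

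**Who sees what.** Under Ethics, a research nurse or research associate approaches the mothers. Under Treatment of Participants, the researchers check use of the allocated teats and supply Calma teats to the intervention group. The monitored-feed form (Appendix E) records the teat type.

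**The concern.** An eligibility rule should use only what is known when the infant is allocated. Here the rule refers to respiratory status in the week after recruitment, when the infant may already have fed from the allocated teat and contributed a primary measurement. If the rule is applied as dated, the arms that are compared are no longer the arms that were randomised.

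The status is not plainly independent of treatment. Trial Aims hypothesises less apnoea and bradycardia with Calmita, so respiratory support a week later could in principle differ by arm. Selecting on it could bias the comparison in a direction that cannot be told in advance.

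The block design is a second, separate route by which selection could enter. A recruiter who can foresee the next allocation can, knowingly or not, influence who is enrolled and when. Being medically stable is partly a judgement, and the nurse may come back later for the mother's decision, so there is some discretion. With 24 evaluable infants planned per arm, a few such infants could move a mean.

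**Working it through.** **1. Order of events, from the text**

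| Week (CGA) | Event | Source |
|---|---|---|
| 33 | Recruitment | Statistical analysis section |
| 33 | Monitored bottle feed with allocated teat | Treatment of Participants, item 2; Table 1 |
| 33 | First primary-endpoint measurement | Trial endpoints |
| 34 | Status that decides the CPAP/ventilation exclusion | Source and Selection of Participants |

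A feed with the allocated teat needs an allocation, so allocation is no later than that feed. Status at 34 weeks cannot be known at 33 weeks.

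**2. The plan's own recruitment figure**

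24 / (1 − 0.20) = 30 per group, which reproduces the plan's number.

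The documents do not say how many infants would be on support at 34 weeks. As an illustration only, assume a fraction x is removed and that this is not already part of the 20% dropout. The number left per group is 30 × 0.80 × (1 − x). Power is for a two-sided independent t-test at 0.05 and the plan's 0.83 SD:

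| x (assumed) | Left per group | Power |
|---|---|---|
| 0% | 24.0 | 80% |
| 3% | 23.3 | 79% |
| 5% | 22.8 | 78% |
| 10% | 21.6 | 76% |
| 15% | 20.4 | 73% |

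The loss of power is modest. The issue is possible bias more than power.

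**3. Predictability with blocks of 4**

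Inputs: block size 4, two arms, 30 per group (so 1:1), 60 infants, hence 60 / 4 = 15 blocks. There are 6 equally likely orders of two and two.

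- The fourth place is always determined. The third is determined when the first two match, which is 2 of 6 orders, or 1/3.
- Expected determined places per block = 1 + 1/3 = 4/3. As a share, (4/3) / 4 = 1/3. Over 15 blocks, 15 × 4/3 = 20 of 60.
- Best guess (always name the arm that is behind, toss a coin when level): place 1, 1/2; place 2, 2/3; place 3, 1/3 × 1 + 2/3 × 1/2 = 2/3; place 4, 1. The sum is 17/6 per block, and (17/6) / 4 = 17/24 = 70.8%, or 42.5 of 60, against 50% by chance.

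**4. Would varied blocks help?**

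The same enumeration gives a best-guess rate of 3/4 for blocks of 2 and 41/60 for blocks of 6. Weighting by block length, with sizes equally likely:

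- 4 and 6: (4 × 17/24 + 6 × 41/60) / 10 = 69.3%
- 2, 4 and 6: (2 × 3/4 + 4 × 17/24 + 6 × 41/60) / 12 = 70.3%

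Allocations known with certainty were simulated over 60 infants, for a recruiter who knows the set of sizes and the full history but not the size of each block. They came to about 6% for 4 and 6, and about 4% for 2, 4 and 6, against 33% now.

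**The case against.** The strongest reply is that no infant is said to be removed. The criterion sits in the selection section, the individual termination criteria do not mention CPAP at 34 weeks, and the analysis is declared intention to treat. The sponsor may simply have worded the timing loosely. This stands in part. A reader might infer that the plan contradicts its own intention-to-treat statement, but the documents do not support that. The conflict arises only if such infants are dropped, and on that the text is silent.

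The moment of randomisation is never stated, and Figure 1 is not shown. Allocation by 33 weeks is a sound inference from two places in the plan, but it remains an inference.

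The number affected is probably small, since infants must be healthy and medically stable. The plan also reports no change in physiological stability with the teat in the sponsor's earlier study. An effect of the teat on respiratory support is therefore possible, not shown. Nor can one say that these losses add to the 20% dropout allowance: dropout is not defined and may already include them.

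On the blocks, 1/3 is what a recruiter gains by following every allocation and block boundary. Anyone less attentive knows less, and foreknowledge is an opportunity for bias, not evidence of it. Nor does the 70.8% best-guess rate argue for varied blocks, because varying the sizes hardly changes it. All of this stands. What remains is that the plan describes no concealment.

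**Conclusion.** The concern holds in a limited form. An exclusion is dated a week later than recruitment, allocated-teat use and the first primary measurement, and the plan does not say how infants who meet it after allocation are treated. Removing them would conflict with intention to treat and would condition on a status that the teat might affect. The conclusion rests on the inference that allocation precedes the 33-week monitored bottle feed. The size cannot be given from the documents and may be small. It would be wrong to conclude that the trial will drop randomised infants or that the arms will be biased.

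The secondary point is that one third of allocations on average (20 of 60) are certain in advance to a recruiter who tracks the blocks, in a single unit where the team that recruits also sees the teats. That is an upper bound on certain foreknowledge, not an estimate of bias.

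**What to change.** **Eligibility.** Reword the CPAP/ventilation criterion so that it is settled at or before randomisation. Add one sentence: any allocated infant on respiratory support at 34 weeks stays in its randomised arm for analysis, with all available feeds. State when randomisation takes place.

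Cost: two or three sentences. Some 34-week feeds will be missing for infants who stay in. Eligibility also shifts slightly: an infant on support at 33 weeks but off it by 34 weeks is not excluded by the present criterion, but could be if the same status were judged at 33 weeks.

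**Allocation.** Say who generates and holds the sequence, and keep it away from those who approach mothers, with each allocation released only after consent and confirmed eligibility. This is the main safeguard. In addition, use randomly varied block sizes (for example 4 and 6, or 2, 4 and 6) that are not disclosed in the protocol.

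Cost: a regenerated list and a short paragraph. The arms may be slightly unequal. Within a block of 6 the difference is at most 3, and after 60 allocations it must be even, so the worst case is 31 against 29.

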## Treatment of Participants

1. When the mother is not available to breastfeed, control group infants will use a conventional teat for suck feeds whereas the interventional group infants will use the Calmita teat. The starter teat will be offered initially and when the infant takes full feeds from the starter teat for 48-72 hours they will then use the advanced teat.
2. Monitoring of a weekly breastfeeds and bottle feeds with the allocated teat will be performed at 33, 34 and 35 weeks CGA and involves the following
  - Weigh infant pre and post breastfeeding
  - Intraoral ultrasound
  - Continuous Intraoral vacuum measurements
  - Respiratory Inductive plethysmography
  - Continuous pulse oximetry for oxygen saturation (SaO2) and heart rate
  - (optional) Maternal pre/post breastfeed milk samples <1.0mL
  - Maternal rating of Preterm Infant Breastfeeding Behavior Scale[5] (PIBBS, Appendix A)

SSB coordination is evaluated using data from intraoral vacuum, respiration and swallowing (Respiratory Inductive Plethysmography) heart rate and oxygen saturation obtained throughout the entire breastfeed[6].

3. Test weights of the infant pre and post feed, for all feeds, will be made to determine milk intake and allow calculation of top up feeds. For monitored feeds, pre and post feed milk samples (<1.0mL) will be collected and fat content measured to provide a further estimate of breast fullness.
4. At each monitored breastfeed the Preterm Infant Breastfeeding Behavior Scale[5] (PIBBS, Appendix A) will be completed by the mother.
5. In the study setting it is assumed that most stable preterm infants are offered (at least daily) breastfeeding experiences from 32 weeks CGA. A weekly breastfeed will be monitored from 33 weeks CGA. At 34 weeks CGA each infant will have up to 2 breastfeeds and one bottle-feed monitored in random order on 2-3 consecutive days with a full or empty breast. A full breast is one that has not been expressed for 3 hours prior to feeding and an empty breast one that has been expressed within an hour of the feed. At 35 weeks CGA those using a nipple shield will have the option of also having a monitored breastfeed without a nipple shield.
6. At 35 weeks or at discharge/transfer each infant will have 1 breastfeed monitored with or without a nipple shield depending on whether the infant is typically feeding with a shield, and one bottle-feed will be monitored. Infants

that remain in the Neonatal Nursery beyond 35 weeks CGA will be invited to continue with weekly monitored breastfeeds and bottle feeds until the time of transfer or discharge.

7. Each week the mother will be given the option of collecting a small milk sample (0.5-1.0mL) before and after every pumping or breastfeed over a 24-hour period to allow more accurate estimation of breast fullness. We expect milk production to increase over the study period therefore one 24-hour collection will not be sufficient.
8. Prior to discharge each mother will be asked to record expression volumes and the milk transfer at the breast (test weigh as in point 5) for a 24-hour period. This will be compared to the normal term infant ranges for 24 hour milk production/milk transfer.
9. At discharge/transfer the mother in the intervention group will receive Calma (term) teats to use for top up feeds while establishing breastfeeding.
10. The mother and infant will be invited to return to KEMH at term corrected age for monitoring of SSB during a breastfeed

The researchers will monitor compliance with use of the allocated teats and pre-post feed weighing during participants' hospital stay, and will be responsible for providing Calma teats to the intervention group mothers prior to the infants' transfer or discharge from KEMH.

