#### Objectives:

1. To track maturation of intraoral vacuum, SSB coordination and physiological stability over time and determine if this is related to increased breastfeeding effectiveness and efficiency.
2. To explore the effect of breast fullness on milk transfer at 34 weeks corrected gestational age (CGA).
3. To explore the use of a nipple shield on milk transfer at 35 weeks CGA.
4. To compare SSB coordination and maturation during breastfeeding with that during bottle feeding with Calmita, and bottle-feeding with a conventional teat.
5. To determine the effect of a vacuum triggered teat on timing of achievement of full breastfeeding and on breastfeeding duration

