### Trial Aims

1. To track maturation of intraoral vacuum and SSB coordination as well as physiological stability of breastfeeding preterm infants over time and determine if this is related to increased effectiveness and efficiency of breastfeeding. We hypothesize that improvement in breastfeeding efficiency (mL/min) and effectiveness (total mL transferred) will be associated with changes in one or more of vacuum strength (average and changes across a feed), consistency of sucking (number of sucks/suck bursts per feed) and SSB coordination.
2. To explore the effect of the volume of milk in the breast on milk transfer during breastfeeding at 34 weeks CGA. Our hypothesis is that more milk in the breast will result in a higher volume of milk being transferred by the infant at the breastfeed.
3. (Optional) To explore the effect of nipple shield use on milk transfer at 35 weeks CGA. The hypothesis is that nipple shields improve attachment and breastmilk transfer
2. To compare SSB coordination and maturation during breastfeeding with bottle feeding with a Calmita teat, and bottle-feeding with a conventional teat. Our hypothesis is that infants fed with a Calmita teat will experience less apnoea and bradycardia and reach full oral feeds more rapidly than those fed with a standard teat.
3. To determine the effect of a vacuum triggered teat (Calmita during stay in study hospital, and Calma used for top up feeds post discharge/transfer from the study hospital) on the timing of achievement of full breastfeeding and on breastfeeding duration.

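### The exploratory nipple-shield aim compares feeds by habitual use: the 35-week with/without pair has no stated order, and one yes/no term mixes within-infant and between-infant differences

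*Combined protocol and SAP*

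**What the plan says.** The Objectives set the question: "To explore the use of a nipple shield on milk transfer at 35 weeks CGA". Trial Aims marks this aim as optional but gives it a direction: "The hypothesis is that nipple shields improve attachment and breastmilk transfer".

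Treatment of Participants, point 6, fixes shield status at the standard 35-week feed: "each infant will have 1 breastfeed monitored with or without a nipple shield depending on whether the infant is typically feeding with a shield". Point 5 adds the only deliberate contrast: "At 35 weeks CGA those using a nipple shield will have the option of also having a monitored breastfeed without a nipple shield". Table 1 agrees, entering the no-shield feed as "Invited if shield normally used". No shielded feed is offered to infants who do not use a shield.

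For 34 weeks, point 5 states the order: "up to 2 breastfeeds and one bottle-feed monitored in random order on 2-3 consecutive days". The text has no matching statement for the 35-week pair. The Trial Plan in the summary is broader than Table 1 and points 5 and 6. It describes monitored feeds "at 35 weeks CGA (with and without a nipple shield", as if the pair applied to infants generally.

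The analysis section uses linear mixed models with random effects grouped by participant, and says: "Use of nipple shield (yes/no), breast fullness (full/empty) and relevant demographic variables will be considered as predictive factors". It does not split the shield term into within-infant and between-infant parts, and it gives neither an order term nor a paired analysis for this aim.

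**The concern.** Shield use is not assigned. The Background says shields may be used to help a preterm infant attach and to improve transfer, and the Ethics section says they are often advised as an aid to attachment. It is therefore plausible that users would feed less well than non-users if neither had a shield.

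A random intercept does not remove that difference. It treats infant ability as unrelated to shield use and takes a weighted average of two quantities: the change within infants fed both ways, and the difference between users and non-users. Only the first is a shield effect. The second also carries the reason for shield use.

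The paired feeds avoid this problem, but without a randomised order any systematic change from the first feed to the second is counted as a shield effect. At stake is a useful shield that appears to do little or, under stronger assumptions, to do harm. The Ethics section describes the current evidence for shield advice as little or none and hopes the findings will inform feeding policy.

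**Working it through.** The plan gives no precision or power figure for the shield comparison, so there is none to reproduce. Its 5 mL difference is defined for full against empty breasts and is borrowed here as the true shield benefit.

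**Inputs**
- From the plan: 24 infants per group after dropout, so 48; breastfeeds at 33 weeks (1), 34 weeks (2) and 35 weeks (1).
- Assumed: 40% shield users (19 of 48); half of them accept the extra feed (10 pairs); between-infant SD 6 mL; within-infant SD 7 mL; shield status otherwise constant; true benefit 5 mL. Users would transfer d mL less than non-users if neither had a shield, with d = 0, 5 or 10.

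**Step 1: within-infant information.** An infant with 4 shielded feeds and 1 unshielded feed contributes 4 - 4²/5 = 0.8. Ten pairs give 10 × 0.8 / 49 = 0.163.

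**Step 2: between-infant information.** The variance of an infant's mean is 36 + 49/4 = 48.25 with 4 feeds and 36 + 49/5 = 45.8 with 5. Mean shield use is 0 for 29 non-users, 1 for 9 users without a pair and 0.8 for 10 users with one. With weights w = 1/variance:
- Σw = 38/48.25 + 10/45.8 = 1.006
- Σwx = 9/48.25 + 8/45.8 = 0.361
- Σwx² = 9/48.25 + 6.4/45.8 = 0.326
- Information = 0.326 - 0.361²/1.006 = 0.197

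**Step 3: the blend.** The between-infant share is 0.197/(0.197 + 0.163) = 0.55. The users' weight is 9/48.25 + 10/45.8 = 0.405, so the between-infant slope carries a bias of -d × (0.361 - 0.361 × 0.405/1.006)/0.197 = -1.10d. The pooled coefficient is about 5 - 0.55 × 1.10 × d = 5 - 0.60d, which gives 5.0, 2.0 and -1.0 mL.

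**Step 4: adjust for week.** Exact generalised least squares with week as a category gives about 5 - 0.63d.

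| User deficit d | Pooled coefficient | Within-infant coefficient |
|---|---|---|
| 0 mL | 5.0 | 5.0 |
| 5 mL | 1.8 | 5.0 |
| 10 mL | -1.3 | 5.0 |

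The pooled value crosses zero at d = 5/0.63 = 7.9 mL. The SD of the estimate is 1.7 mL pooled and 2.6 mL within-infant. For the 35-week pairs alone it is √(2 × 49/10) = 3.1 mL with 10 pairs and 3.3 mL with 9, so about 3.2 mL.

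**Step 5: vary the assumptions.** Simulation over user share 30-50%, uptake 25-100%, intraclass correlation 0.3-0.5 and total SD 7.0-13.2 mL, with the true benefit kept at 5 mL, gave these mean pooled coefficients:
- d = 0: about 5 mL
- d = 5: 0.7 to 3.8 mL
- d = 10: -3.7 to 3.0 mL
- d = 14.5: -7.4 to 2.9 mL

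Mean within-infant estimates stayed between 4.1 and 5.6 mL.

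**Step 6: order.** If the unshielded feed always came second and transfer rose 3 mL (assumed) for that reason alone, the paired difference would be 5 - 3 = 2 mL. If it always came first, the difference would be 5 + 3 = 8 mL.

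**The case against.** Much can be said for the plan.

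- **The aim is optional and exploratory.** It is not the teat comparison, and the trial was not sized for shield pairs. This stands and limits the weight of the point.
- **No deficit is documented.** Shields used to aid attachment could also be in broad routine use. With no deficit the pooled coefficient is unbiased and the more precise estimate. This stands: every biased figure above is conditional.
- **The benefit may exceed 5 mL.** The means the plan cites differ by 18.4 - 3.9 = 14.5 mL. With a benefit that large, a 10 mL deficit would leave 14.5 - 6.3 = 8.2 mL, which is shrunken but not reversed.
- **Status may change between weeks.** The master case report form has with-shield and without-shield columns for each week. If half of users stopped partway, the 10 mL case would move from about -1.4 to +0.2 mL. The bias is smaller but remains, and stopping may itself follow maturation.
- **Timing and fullness are partly covered.** The Trial Plan can be read as applying its two-day window to 35 weeks as well. Fullness is recorded at each monitored breastfeed and listed as a predictor. What is missing is the order, not every control.
- **The model is not fully specified.** Shield use is to be considered as a predictor. A single unsplit term is the natural reading, not an explicit commitment.

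A reader might infer that these infants depend on the shield, or that it was given because they attached poorly. The documents speak only of using it, or of normally or typically feeding with it. Figure 1 is not available, so the absence of a stated order applies to the text alone.

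**Conclusion.** The point holds in a limited form. Shield status follows habit, the 35-week pair has no stated order, and the planned term combines a within-infant effect with a difference between kinds of infant. Under the base assumptions, each 1 mL by which users are weaker feeders takes about 0.63 mL off the estimated benefit. A 5 mL deficit turns a true 5 mL into 1.8 mL, and a 10 mL deficit into -1.3 mL.

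A reader might conclude that the shield result will be reversed. The documents do not support that. Reversal needs a deficit clearly above the benefit (about 7.9 mL against 5 mL in the base case), and even then some settings in the wider range keep a positive sign. User share, uptake, variances, deficit and order effect are all assumed.

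Nor does the design make the aim worthless. Removing the shield from habitual users is a legitimate contrast for those infants, though it does not show what introducing a shield would do in others. Because the correction is cheap and uses feeds already planned, it is worth making even for an exploratory aim.

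**What to change.** 1. **Treatment of Participants, point 5.** Among mothers who opt in, randomise the order of the 35-week feeds with and without a shield, as is done at 34 weeks, preferably with both feeds in the same recorded fullness category.
2. **Statistical analysis section.** Split shield use into within-infant and between-infant parts, for example by adding each infant's mean shield use to the model. Base the shield aim on the within-infant coefficient, with the paired 35-week difference as a sensitivity analysis. Do not read the between-infant part as a shield effect.
3. **Trial Aims and Trial Plan.** State that the estimate applies to infants who habitually use a shield, and reconcile the Trial Plan with Table 1 and points 5 and 6.

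This needs wording and an order list, with no added feeds. The price is precision and a narrower claim: under the base assumptions the SD of the estimate rises from 1.7 mL pooled to 2.6 mL within-infant, or to about 3.2 mL from the pairs alone. That is why the pairs should support the estimate and not replace it. On root mean squared error, the pooled term would still win for small deficits: √(2.62² - 1.70²) = 2.0 mL, and 2.0/0.63 is a deficit of about 3.2 mL. At a 5 mL deficit its error is √(3.2² + 1.7²) = 3.6 mL, against 2.6 mL within-infant.
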